## 1. Study information

### 1.1. Description (optional)

Autism spectrum disorder (hereafter ‘autism’) is a neurodevelopmental condition that is characterised by difficulties in social communication and restricted and repetitive interests [1]. Throughout life, autistic people (‘identity-first’ terminology is used throughout in line with the preferences of the autistic community [2] and guidance for avoiding ableist language [3]) experience a higher risk of psychiatric and mental health disorders [4] and elevated risks of premature mortality by nearly two decades than their non-autistic peers [5]. In a population-derived sample of young autistic people aged 10 to 14, 71% met criteria for at least one mental health disorder, with 41% having additional pychiatric diagnoses [6]. Similarly high rates of mental health problems have been found in other studies of autistic adolescents [7] and autistic adults [8–11]. Two of the most common psychiatric problems for autistic adults are depression and anxiety [12–15], with prevalence rates for depressive and anxiety disorders reaching as high as 47.1% and 54.0%, respectively [16]. It is also possible that prevalence rates of co-occurring psychiatric and mental health difficulties are underestimated, with many autistic individuals being subject to missed, delayed or inaccurate diagnoses [17] and healthcare needs which remain unmet in health systems modelled on the needs of neurotypical individuals [18].

For autistic individuals, mental health difficulties increase the likelihood of poorer long-term outcomes [19] including lower social and adaptive functioning [10], educational and employment difficulties [20, 21], poorer quality of life [22–24], and suicidality [25]. In order to support autistic people in achieving positive long-term outcomes, it is important to further understand the presentation of mental ill-health in autism and to determine *why* autistic individuals are at higher risk of mental health difficulties. This is crucial since the mental health of autistic individuals has been identified as a key priority for research across multiple stakeholder groups [26, 27].

There are many factors that could contribute to elevated mental health difficulties in autism. For example, since the prevalence of alexithymia (a subclinical condition characterised by difficulties identifying, expressing and differentiating emotions [28]), a transdiagnostic risk factor for numerous psychiatric conditions (e.g., depression, [29], and anxiety disorders, [30]) is higher in the autistic [49.93%] than the non-autistic population (4.89%; [31]), alexithymia may lead to increased risk of mental health difficulties in autism. Alternatively, Botha and Frost [32] advocate the extension of the minority stress model to explain the substantial health disparities between autistic and non-autistic individuals. The minority stress model posits that high stress burdens can negatively impact the mental and physical health of marginalised groups [33]. Such stress burden and resulting poorer health is frequently observed in minority groups including sexual, gender identity and ethnic minorities [34, 35], and minority stressors have recently been described to increase depressive symptoms in those with physical disabilities [36]. Examples of minority stressors include everyday discrimination, internalised stigma, and concealment. In line with this, the current study focuses on the impact of autism acceptance and camouflaging (which are minority stressors) on the mental health of autistic individuals (a marginalised group).

#### 1.1.1. Autism acceptance, camouflaging and mental health

Autism acceptance, as discussed here, can be defined as “an individual feeling accepted or appreciated as an autistic person, with autism positively recognised and accepted by others and the self as an integral part of that individual” [37]. The majority of autistic individuals in the UK feel that society does not accept [43%] or only sometimes accepts [48%] them as an autistic person (in total 91%; [37]). In spite of this, until recently, research had not directly examined autistic people’s experiences of autism acceptance and how this relates to mental health difficulties. The first study to do so confirmed an association between acceptance and mental health, finding that autism acceptance from external sources predicted depression and stress [37] and personal acceptance predicted depression. In addition, individuals who spontaneously reported camouflaging their autistic traits also reported higher symptoms of depression and fewer experiences of acceptance in the past week [37].

Camouflaging can be defined as “the use of strategies by autistic people to minimise the visibility of their autism in social situations” [38]. These strategies can involve compensation, whereby autistic individuals develop behaviours to help them manage social situations (e.g., learning how to use eye contact or developing scripts to help them navigate social interactions; [38, 39]), and masking, whereby autistic individuals aim to hide their autistic traits (e.g., deliberately suppressing stimming behaviours; [38]). Whilst the vast majority of autistic individuals report camouflaging to some degree [38], there are indications that camouflaging may be more common among women [40–48] and those higher in autistic traits [40, 49–51]. There is inconsistent evidence regarding whether camouflaging is associated with broader cognitive ability [40], with some studies finding that a higher level of education is associated with greater camouflaging [49], and others suggesting there is no association between Intelligence Quotient (IQ) and camouflaging [38, 42, 52] or executive functioning and camouflaging [48].

However, a burgeoning literature suggests that camouflaging may be a risk factor for depression and anxiety in autism [25, 37, 53–57], irrespective of gender [58]. Interestingly, Cage and colleagues [37] suggest that camouflaging may mediate the relationship between social stressors (e.g., lack of autism acceptance, bullying) and anxiety and depression. That is, those who experience more social stressors (such as a lack of autism acceptance) are more likely to camouflage their autistic traits, which in turn results in higher levels of anxiety and depression. However, a recent study found that whilst autism-related stigma was associated with lower wellbeing, camouflaging did not mediate this relationship (despite camouflaging being positively associated with autism-related stigma; [59]). Future research should verify whether camouflaging mediates the relationship between autism acceptance/stigma and anxiety and depression more specifically.

It is important to note that the terms we use to refer to camouflaging vary across the globe [60]. In Japan, the term ‘over-adaptation’ is used to describe excessive efforts made by people (i.e., society more broadly) to meet external demands and expectations, even if this means forcibly suppressing their internal needs [61]. In recent years, this term has been applied to autism to describe the substantial efforts made by autistic people to fit into an environment as a result of differences in interpersonal and social behaviour [62–64]. As such, this concept is highly similar to the construct of camouflaging (see [61] for a discussion around the similarities and differences between the constructs of camouflaging and over-adaptation in autism). Importantly, there is anecdotal evidence that over-adapatation is associated with poorer mental health in autistic individuals in Japan [65]. However, to date no empirical studies have tested this relationship [61], and therefore further study of over-adaptation and camouflaging in Japan is necessary.

#### 1.1.2. Cross-cultural perspectives on autism acceptance, camouflaging and mental health

Culture can be defined as “a set of basic assumptions and values, orientations to life, beliefs, policies, procedures and behavioural conventions that are shared by a group of people” [66]. Unsurprisingly, across different cultures there can be large variation in these beliefs, attitudes and behaviours. In the case of autism, we see cross-cultural variation in attitudes towards autistic people: previous research has found that *non-autistic* college students in the US reported lower levels of autism-related stigma than their Lebanese [67, 68] and Japanese [69] counterparts. Whilst these studies demonstrate that there may be variation in levels of autism stigmatisation among *non-autistic* individuals across cultures, studies have not yet compared *autistic* individuals’ experiences of autism acceptance across different cultures. Given that levels of stigma reported by non-autistic individuals vary cross-culturally, it is plausible that experience of acceptance from the perspective of autistic individuals themselves also vary across cultures. Such cross-cultural differences may exist in both external acceptance (as experiencing stigma may result in autistic individuals feeling less accepted by others) and personal acceptance (as stigma can become internalised resulting in decreased personal acceptance or ‘self-stigma’; [54, 70, 71]).

As Lai and colleagues [72] highlight, it is paramount to determine the levels of camouflaging in the autistic population. Currently, it is unknown how many undiagnosed autistic adults exist [73]. However, it is thought that there are more undiagnosed autistic individuals in some areas of the world than others [74]. Investigating the rates of camouflaging across cultures will help us to work towards determining the true prevalence of autism, and its sex/gender ratio, across the globe. To our knowledge, studies have not yet explored camouflaging in autistic populations outside of the UK (e.g., [58]) and USA (e.g., [75]), though there are anecdotal reports of over-adaptation in Japan. Rather than assuming levels of camouflaging in the UK and USA reflect those globally, researchers should collaborate internationally to compare camouflaging behaviours cross-culturally. Cross-cultural perspectives could have great utility for understanding the mechanisms behind camouflaging, as the social environments in which autistic individuals aim to adapt to vary across cultures. For example, by determining whether the rates of camouflaging are higher within certain cultures, we can work towards identifying socio-cultural factors that may contribute to camouflaging. This is important as there is a consensus among researchers that ‘there is much to be learnt about mechanisms’ [72].

Whilst no research has compared camouflaging across cultures, it seems likely that rates of camouflaging will vary between cultures for a number of reasons. Firstly, in collectivist cultures (which prioritise community interdependence and shared group norms and values; [76]), there may be more pressure relative to individualistic cultures (which prioritise independence and individualism; [76]) to camouflage one’s autistic traits in order to minimise deviation from shared group norms. Thus, those in collectivist cultures may alter their behaviour or hide their autistic traits in order to avoid shame and fit in [62]. In contrast, in regions where there are more discussions about neurodiversity- both as a movement and as an ideology (e.g., the United States, Canada, and the United Kingdom; see [77])- individuals may feel less pressured to camouflage their autistic traits. Finally, since autism-related stigma varies across cultures [67–69] and reduced autism acceptance is associated with increased camouflaging [34, 61], levels of camouflaging may also differ cross-culturally.

Moreover, to the best of our knowledge, studies have not yet compared the level of mental health difficulties in cross-cultural samples of autistic individuals. Like camouflaging, there are reasons to believe there is cross-cultural variation in the level of these difficulties. Firstly, since autism acceptance differs across cultures [67–69], the level of mental health difficulties may also vary because a lack of autism acceptance or stigma is associated with poorer mental health [32, 37]. Secondly, since beliefs about mental health vary across cultures [78], and these beliefs can affect willingness to seek and adhere to treatment [79], there may be cross-cultural differences in levels of mental health difficulties. Finally, given that accessibility of mental health services also differs across cultures [80], individuals from certain regions may be unable to get the help they need, thus leading to poorer mental health. Research is necessary to explore whether the levels of mental health difficulties experienced by autistic individuals vary across cultures.

#### 1.1.3. The current study

In the current study, we aim to replicate the regression analyses from previous research that found a) depression was predicted by external and personal acceptance, and stress was predicted by external acceptance [37], b) camouflaging was predicted by stigma [59], and c) anxiety was predicted by camouflaging [58] (whilst controlling for relevant participant characteristics, e.g., age, gender, etc.) in a more representative sample of autistic adults. In addition, we aim to compare autistic individuals’ experiences of autism acceptance, camouflaging and mental health across multiple countries: Australia, Belgium, Canada, Japan, South Africa, the United Kingdom, and the United States. Importantly, exploring these factors across cultures has the potential to a) elucidate the potential routes to greater autism acceptance, reduced need for camouflaging behaviours and improved mental health outcomes, b) identify ‘priority regions’ for anti-stigma interventions (like those in Ranson and Byrne, [81] and Gillespie-Lynch et al., [82]), and c) highlight areas where greater support for mental health difficulties is needed. In addition, since acceptance is likely to vary across cultures, we are employing an experimental design which naturally maximises variation in autism acceptance, thus giving us the ability to more sensitively assess the impact of autism acceptance on camouflaging and mental health respectively.

In order to fulfil our aims, participants will complete a number of questionnaires including Autism Acceptance Questions [37], the Camouflaging Autistic Traits Questionnaire [51], and the 21-item Depression, Anxiety and Stress Scale (DASS-21; [83]). Participants will also provide demographic information (e.g., age, sex assigned at birth, gender identity, sexual identity, ethnicities, country of birth, country of residence, years lived in country of residence, number of siblings, level of education, income, autism diagnosis, person/team that gave them their diagnosis, age of autism diagnosis, co-occuring diagnoses, how verbal they would consider themselves now, and how verbal they were as a child).

### 1.2. Hypotheses (required)

#### 1.2.1. Replicating the regression analyses from previous research

First, we will conduct regression analyses on our data as a whole (i.e., participant data will be analysed as one large and diverse group) to replicate the findings from previous studies [37, 58, 59] in a more diverse sample. In line with Cage and colleagues [37], we predict that external acceptance and personal acceptance will contribute to depression scores, after controlling for age, gender, age of diagnosis, anxiety scores and stress scores. In addition, we predict that external acceptance will contribute to stress scores, after controlling for age, gender, age of diagnosis, anxiety scores and depression scores. As was the case in Perry et al., [59], we hypothesise that autism acceptance will predict camouflaging scores after controlling for age, gender, age of diagnosis, and autistic traits. In line with Hull et al., [58] we predict that camouflaging will contribute to anxiety scores after controlling for age and autistic traits.

#### 1.2.2. Comparing levels of autism acceptance, camouflaging and mental health across cultures

Finally, we will separate participants into groups based on their country and use a between-subjects multivariate analysis of variance (MANOVA) to explore participants’ experiences of autism acceptance, camouflaging, and levels of depression, anxiety and stress (dependent variables) across these countries (independent variable). We predict that there will be differences in the level of autism acceptance across countries. In addition, we aim to explore whether there are any differences in the level of camouflaging and mental health difficulties across countries.

## 2. Design plan

*In this section, you will be asked to describe the overall design of your study. Remember that this research plan is designed to register a single study, so if you have multiple experimental designs, please complete a separate preregistration*.

### 2.1. Study type (required)

Observational Study—Data is collected from study subjects that are not randomly assigned to a treatment. This includes surveys, natural experiments and regression discontinuity designs.

### 2.2. Blinding (required)

No blinding is involved in this study.

### 2.3. Study design (required)

This study employs a between-subjects design, where we will be comparing participants experiences of personal acceptance, external acceptance, camouflaging, depression, anxiety and stress across cultures.

### 2.4. Randomization (optional)

No randomization is involved in this study.

## 3. Sampling plan

*In this section we’ll ask you to describe how you plan to collect samples, as well as the number of samples you plan to collect and your rationale for this decision. Please keep in mind that the data described in this section should be the actual data used for analysis, so if you are using a subset of a larger dataset, please describe the subset that will actually be used in your study*.

### 3.1. Existing data (required)

Registration prior to creation of data: As of the date of submission of this research plan for preregistration, the data have not yet been collected, created, or realised.

### 3.2. Data collection procedures (required)

Participants will be recruited via an existing international autism research database kept by the U21 Autism Research Network. The database was set up as part of a collaboration between seven autism research groups across 4 continents and 7 countries (Australia, Belgium, Hong Kong, Japan, New Zealand, UK, and USA). The aim of this initiative was to diversify samples recruited for autism research and to generate opportunities to answer questions relevant to the global autistic community. In this particular study, we will be recruiting participants from our sites in Belgium, Japan, UK and USA. In addition, we will recruit participants via Prolific, thus allowing us to recruit participants from Australia, Canada, and South Africa (amongst others), and via social media. All participants will provide informed consent. This study has been approved by the Science, Technology, Engineering and Mathematics (STEM) committee at the University of Birmingham (ERN_16-0281AP9D).

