### 3.3. Sample size (required)

The final sample in this study will comprise at least 286 autistic adults (aged over 18) from across the globe.

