#### 3.4.2. Comparing autism acceptance, camouflaging and mental health across cultures

In the analyses where we will compare participants’ experiences of autism acceptance, camouflaging, and levels of depression, anxiety and stress across countries, we will only include data from countries that have at least 30 participants (and therefore we will have sufficient data to draw comparisons between these multiple groups). We selected this cut-off as Sekaran [87] highlights that “where samples are to be broken into sub-samples…a minimum sample size of 30 for each category is necessary”. Importantly, Sekaran [87] also highlights that “in multivariate research…the sample size should be several times (preferably 10 times or more) as large as the number of variables in this study”. By recruiting at least 286 participants to our study, our sample is over 47 times larger than the number of variables in our multivariate analysis (6 variables: external acceptance, personal acceptance, camouflaging, depression, anxiety and stress), is as large as necessary based on our power analyses (largest sample size generated = 286), and would facilitate comparisons between participants in up to 9 countries.

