#### 5.1.2. Comparing autism acceptance, camouflaging and mental health across cultures

Finally, in order to compare participants’ experiences of autism acceptance, camouflaging, and levels of depression, anxiety and stress across countries, we will use a multivariate analysis of variance (MANOVA). This MANOVA will have the between-subjects factor *country* and the dependent variables *external acceptance*, *personal acceptance*, *depression*, *anxiety*, *stress*, and *camouflaging*. This will facilitate exploration of group differences in the levels of autism acceptance, camouflaging and mental health difficulties.

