### 5.3. Inference criteria (optional)

For our regression analyses, to account for the four tests we will use a p < .0125 significance threshold to determine whether to accept or reject the null hypothesis. For our MANOVA, we will use a p = .05 significance threshold.

In our analyses, Bayes Factors (BF_01_) may be reported, which provide a ratio of the likelihood for the observed data under the null hypothesis compared to the alternative hypothesis [101]. For all Bayesian analyses, we will follow the classification scheme in JASP outlined by Lee and Wagenmakers [102]: BF_10_ values between one and three will be considered as weak evidence, between three and ten as moderate evidence and greater than ten as strong evidence for the alternative hypothesis.

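### Recruitment route is partly tied to country but appears in no country model, so any difference between routes can be reported as a cultural difference

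*Protocol article*

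**What the plan says.** Section 3.2 of the protocol article describes three routes. The first is an international autism research database: "In this particular study, we will be recruiting participants from our sites in Belgium, Japan, UK and USA". The second and third, Prolific and social media, follow in the next sentence: "In addition, we will recruit participants via Prolific, thus allowing us to recruit participants from Australia, Canada, and South Africa (amongst others), and via social". No route is assigned exclusively to any country. Australia belongs to the database network but, for this study, is named only under Prolific.

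Section 5.1.2 defines the country comparison: "This MANOVA will have the between-subjects factor *country* and the dependent variables" external acceptance, personal acceptance, depression, anxiety, stress and camouflaging. Section 5.3 sets the test level: "For our MANOVA, we will use a p = .05 significance threshold". Section 3.4.2 restricts the comparison: "we will only include data from countries that have at least 30 participants".

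Section 5.6 repeats the MANOVA with adjustment for individual differences that relate to the outcomes or differ between groups. Its examples include autistic traits, alexithymia, gender, education, age at diagnosis and income. Country differences that remain are to be read as cultural. Route is not among the participant questions in 4.2.1 and is in no model. Among the uses that 1.1.3 says the cross-cultural comparison could serve is to "identify ‘priority regions’ for anti-stigma interventions".

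**The concern.** People on an autism research register, members of a commercial online panel and people reached through social media may differ in acceptance, camouflaging or distress wherever they live. If the mix of routes differs between countries, such a difference moves the country means, and a one-factor MANOVA cannot tell the two sources apart.

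The comparison across countries is one of the study's two stated aims (1.1.3), and 1.2.2 predicts that acceptance will differ between countries. At stake is whether a significant country effect can be attributed to country at all. The residual MANOVA across countries in 5.6 is exposed in the same way. Data had not been collected when the plan was registered (3.1). A country recruited by one route only cannot be repaired afterwards.

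**Working it through.** **The plan's own sizing.** Section 3.3 states: "The final sample in this study will comprise at least 286 autistic adults". With 6 outcomes, 286/6 = 47.7. With at least 30 per country, 286/30 = 9.5, so up to 9 countries. Both figures in 3.4.2 reproduce. Neither bears on route.

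**Assumptions, not in the article.** 7 countries of 41 (286/7 = 40.9); no true country effect; outcomes correlated 0.3 in absolute value; a route shift of δ SD on the three DASS scales; social media given no share. Three countries are mainly Prolific, two mainly database, and the UK and USA half each.

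**How the mix drives the size.** For a Wilks MANOVA the spurious country signal is approximately

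λ = n · Σ(s_c − s̄)² · D²,

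where s_c is the Prolific share in country c and D² is the squared standardised distance between routes. For three shifted outcomes out of six with correlation 0.3, D² = (δ²/0.7)·(3 − 0.3·9/2.5) = 2.743δ². That is 0.247 at δ = 0.3 and 0.686 at δ = 0.5.

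- Shares 1, 1, 1, 0, 0, 0.5, 0.5: s̄ = 4/7 = 0.571. The sum of squares is 3(0.429)² + 2(0.571)² + 2(0.071)² = 1.214, and 41 × 1.214 = 49.8.
- 90/10: every deviation is multiplied by 0.8, so 49.8 × 0.64 = 31.9.
- 70/30: every deviation is multiplied by 0.4, so 49.8 × 0.16 = 8.0.

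**Simulated rejection at .05, no country effect**

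| Route mix | λ at 0.3 / 0.5 SD | Rejection at 0.3 / 0.5 SD | Longer run (5,000 per setting) |
|---|---|---|---|
| 100/0 | 12.3 / 34.1 | 35% / 88% | 35% / 88% |
| 90/10 | 7.9 / 21.9 | 22% / 57% | 21% / 60% |
| 70/30 | 2.0 / 5.5 | 6% / 11% | 8% / 14% |
| Same mix in every country | 0 / 0 | – | about 5% |

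The two sets of runs agree to within about 3 points. With no route shift, the longer run rejects in about 5% under every mix. At 100/0 a shift of only 0.2 SD gives about 14–15%.

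**If only one outcome shifts** (100/0 mix, correlation 0 or 0.4), a separate simulation gives 8–10% at 0.2 SD, 13.5–18% at 0.3 SD and 36–55% at 0.5 SD.

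**What adjustment can do.** In that one-outcome setting, with UK and USA recruited by both routes and correlation 0.4, unadjusted rejection at 0.2, 0.3 and 0.5 SD is 9%, 18% and 55%. With route as a covariate it is 4.5%, 5.1% and 4.9%. If every country had a single route (four database, three Prolific), the design matrix has rank 7 with or without route. No model could then separate route from the contrast between the two sets of countries.

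**The case against.** The strongest reply is that the tie between route and country is not established. Section 3.2 introduces Prolific as an addition, says the three named countries are among others, and places no country limit on social media. Nothing makes Belgium or Japan database-only, or Australia, Canada or South Africa Prolific-only. At a 70/30 mix the inflation is modest. This stands, and it is why the size has to be shown across mixes.

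Second, the article documents no route difference, so the harm is conditional. This also stands.

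Third, the adjusted MANOVA in 5.6 would remove whatever part of a route difference runs through measured characteristics such as education, income or age at diagnosis. That is true, but the rest would remain and would be read as cultural.

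Fourth, 4.2.1 lists questions put to participants, whereas recruitment source is administrative information that could be held elsewhere. A reader might infer that the data needed to check route would not exist; the article's silence does not show that. It does show that no stated analysis uses route.

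Fifth, 1.1.3 speaks only of a potential to identify priority regions, and the camouflaging and mental-health comparisons are framed as exploration; only the acceptance difference is predicted. That limits how much weight the DASS-based figures carry, but the same mechanism applies to acceptance. Naming Australia only under Prolific is a choice for this study, not a contradiction.

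**Conclusion.** The concern holds in conditional form. Route is partly tied to country, country is the only factor in the MANOVA, and the adjusted version covers individual differences only. If routes differ on the outcomes, the plan as written can report that difference as cultural.

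With shifts of 0.3 to 0.5 SD on the DASS scales, false rejection runs from just above the nominal 5% at a 70/30 mix to about 88% when three countries are all Prolific and two all database. Both the shift and the mix are assumptions.

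A reader might go further and infer that route is almost nested in country, or that a route difference will be reported as culture. The recruitment text leaves room for overlap in every country, and no route effect is documented, so neither inference is supported. This should be fixed; it does not by itself invalidate the country comparison.

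**What to change.** In 3.2, record each participant's recruitment route, for example with a separate survey link per route. Use more than one already available route in each country where possible, for example Prolific and social media; the article lists no database group in Canada or South Africa. Tabulate route by country.

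In 5.1.2 or 5.6, prespecify a sensitivity MANOVA with route as a covariate. Add a comparison within a single route, limited to countries that keep at least 30 participants. That limit matters: with 41 per country and half from Prolific, the UK and USA would each keep about 20, below the plan's own minimum.

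State that contrasts between countries sharing no route cannot be separated from route and will not be interpreted as cultural. A covariate does not rescue those contrasts.

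The cost is one survey field, one or two added analyses, and lower precision in those analyses.
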